### Patient and public involvement (PPI)

During the study protocol development, patient and public groups were involved. A PPI discussion took place, involving people with lived experiences of brain injury, relevant to the project. Individuals were consulted at multiple stages; they reviewed and provided feedback on written study documents, and a further online group discussion took place around the key study aims, data fields and outcomes. Feedback derived from this session was incorporated into and influenced aspects of the proposed methodology and outcomes. The PPI groups influenced the study design with regards to the overall study aims and study outcomes.

### Eligibility criteria

The study will include patients of any age meeting the case definition criteria and admitted to a participating institution with an sICH during the selected 30-day study period. The case definition is:

patients of any age with the presence of sICH (IPH, intraventricular haemorrhage and/or SAH haemorrhage) on intracranial imaging, in the absence of a definite history of head trauma, or other clinical features highly suggestive of head trauma;hospital admission for sICH management. This includes admission for observation, conservative or interventional management to both ward-based and critical care settings.

A patient will be included in the final analysis if>70% of the data fields required have been recorded.

Exclusion criteria are as follows:

patients who have a clear history of head trauma as the primary cause of the haemorrhage and, therefore, are diagnosed with traumatic intracranial haemorrhage;patients with subdural or extradural haematomas but no clear history of trauma;patients with intracranial haemorrhage occurring as a complication of a procedure or intervention (eg, postoperative haematoma) or iatrogenic (eg, after thrombolysis for ischaemic stroke);patients who are admitted for elective (planned admission to hospital) or semielective (where a patient was initially admitted to hospital, then discharged from hospital and readmitted for surgery) procedures;patients readmitted to hospital within 30 days of the initial admission with sICH (including those readmitted for acute management of sICH-related complications);patient presenting to the emergency department (ED) but discharged home from the ED immediately without a period of observation or admission to a ward.

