### Study setting and population

The study will recruit centres worldwide through pre-existing research networks and collaboratives, developed through the National Institute for Health and Care Research Global Health Research Groups on Neurotrauma and Acquired Brain and Spine Injury. Invitation to participate will also be extended through relevant professional societies and academic groups.

Any hospital admitting patients with sICH worldwide is eligible to participate. A minimum of one case must be submitted by each site during the 30-day chosen study period. At each site, the local team will comprise a local lead, up to two additional data collectors, a data validator and supervising clinician. The study recruitment is planned to run for a total of 12 months (February 2025–January 2026). Eligible patients presenting with sICH over a consecutive 30-day period chosen by each individual recruiting centre during the overall study period will be enrolled. Patients will be followed up until 30 days, death or discharge from hospital, whichever comes first. All data will be submitted to the central study team for inclusion in the final dataset. A minimum sample size of 712 patients will be recruited, as detailed in the Statistical Analysis section below.

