### Data collection and storage

Data will be collected from consecutive patients who met the inclusion criteria during the study period. The dataset contains five sections: baseline data, imaging data, acute management data, operative or interventional data (if applicable) and outcome data (see online supplemental material). The data points were determined through consultation with clinicians from a range of income settings. Only pseudonymised data will be collected on the online platform, and anonymised data will be accessed by the central study team.

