#### Outcome measures

The primary outcome of the study is 30-day mortality or survival to hospital discharge (whichever comes first). Participating centres will be stratified according to income settings, and mortality rates will be compared across cohorts defined by income groups.

Secondary outcome measures include:

perioperative complications, including but not limited to surgical site infections;clinical outcomes other than mortality, measured through:Glasgow coma scale at discharge;modified Rankin scale.Length of hospital stay and intensive care unit stay.

Each unit will be asked to complete a questionnaire on care processes and resources available. This will describe local case load, catchment population and referral pathways, and management frameworks and infrastructure at prehospital and hospital level.

Data will be collected and stored exclusively on a secure web-based system within the Outcome Registry Intervention and Operation Network platform https://orion.net/. This will enable secure data collection, validation and storage in a standard format, which is compliant with the UK National Health Service (NHS) security standards (including the Information Governance Toolkit). All patient data will be recorded and held anonymously. A pilot phase was conducted to assess feasibility prior to rolling out the full study.

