### Statistical analysis

A formal a priori statistical plan will be produced for data analysis. In short, the primary analysis will comprise statistical descriptive analysis of patient-level variables and the characterisation of processes of care using descriptions of provider profiling data and patient-level process variables.

Country groups will be defined using the human development index (HDI), a recognised index of human development.^21^ The 30-day mortality will be reported for each HDI tier. Further analyses will stratify against other indices of economic development and health. Multivariable logistic regression models will be used to investigate the primary and secondary outcomes. Provider profile summaries will be compared with current evidence-based best practices to identify gaps and associations with care processes and case mix.

There is limited robust epidemiological data on sICH globally across income settings, with mortality rates for hospital cohorts reported between 20% and 33% in HICs and 39% and 62% in LMICs.^22^,^28^ Therefore, an accurate sample size calculation is not feasible. However, taking conservative mortality estimates indicating a 30-day mortality rate for sICH of around 30% in HICs and up to 40% in LMICs, using an alpha value of 0.05 and power of 80% to show a 10% difference between HIC and LMIC settings, a total of 712 patients would need to be recruited. Subgroup analyses will be performed, for example, to describe differences between sICH subtypes or hospital type.

Based on the data and experience from other observational studies with a similar methodology, we would expect that each centre enrols around three to five patients over a 30-day study period.^19^ Therefore, with around 150 recruiting centres from our pre-existing research network, we would expect to meet and exceed the sample size required. Given the nature of this international study, missing values are expected and could affect some participating centres more than others. Patients with at least 70% data field completeness will be included in the analysis. At each site, a data validator, independent from the primary data collectors, will validate accuracy for key study variables to ensure completeness and data accuracy.

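### The 70% field-completeness rule can remove patients with known vital status from the mortality comparison and may bias it, in a direction the protocol does not determine

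*Protocol article*

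**What the plan says.** The completeness rule appears twice in the protocol article. Under Eligibility criteria: "A patient will be included in the final analysis if>70% of the data fields required have been recorded". Under Statistical analysis: "Patients with at least 70% data field completeness will be included in the analysis". The first requires more than 70% and the second accepts exactly 70%. Neither makes an exception for a patient whose outcome is known.

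Under Outcome measures, the primary outcome is mortality up to 30 days or discharge, and "mortality rates will be compared across cohorts defined by income groups". The Data collection and storage section lists baseline and imaging data, followed by "acute management data, operative or interventional data (if applicable) and outcome data", so the count of recorded fields extends well beyond the outcome. The Statistical analysis section also says that "missing values are expected and could affect some participating centres more than others".

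**The concern.** A patient is enrolled on meeting the case definition. Whether that patient is then analysed depends on how much was later recorded across the whole form. For a mortality analysis this is selection after enrolment on something other than the outcome. A death or a survival that is fully known can be dropped because other fields are blank.

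Two things are at stake. First, known primary outcomes are lost from a cohort meant to consist of consecutive patients. Second, if completeness is related to death, the mortality reported for a setting is biased. If that relation differs between settings, the comparison between them is distorted as well. Both are plausible here. The plan expects uneven missingness across centres, and some fields are filled in only as care proceeds, so a patient who dies early may have less recorded. This last step is an inference, not something the article states.

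**Working it through.** **Inputs from the Statistical analysis section.** Mortality 30% in HICs and 40% in LMICs, alpha 0.05, power 80%, total 712. The article gives no exclusion rates, so every exclusion share below is an assumption.

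**Step 1: reproduce the plan's figure.** Two-sided test of two proportions, pooled variance under the null, equal groups:

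n = [1.960 × √(2 × 0.35 × 0.65) + 0.842 × √(0.30 × 0.70 + 0.40 × 0.60)]² / 0.10² = 355.9, so 356 per group and 712 in total.

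Power at 356 per group is 80.0%. The stated size is right for its assumptions, and it contains no allowance for records removed by the completeness rule.

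**Step 2: when the rule causes bias.** Let eD and eS be the shares of deaths and of survivors removed in a setting with true mortality p. Then:

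observed mortality = p(1 − eD) / [p(1 − eD) + (1 − p)(1 − eS)]

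The observed odds of death equal the true odds times (1 − eD)/(1 − eS). Two results follow.
- Mortality in a setting is biased only if eD and eS differ, that is, if exclusion depends on death.
- The odds ratio between settings is distorted only if (1 − eD)/(1 − eS) differs between settings.

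Three cases show this:
- 10% removed everywhere, unrelated to death: 30.0% v 40.0%, no bias, power 75.7%.
- Setting only (2% removed in HICs, 20% in LMICs, unrelated to death): 30.0% v 40.0%, no bias, power 75.0%.
- Death only (20% of deaths and 5% of survivors removed in both groups): 26.5% v 36.0%. Both rates are too low and the gap is 9.4 points, but the odds ratio stays at 1.56. Power is 73.1%.

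**Step 3: exclusion that depends on death in one setting only.** Assume no HIC exclusions and a share f = 0.20 of LMIC patients dropped, with mortality m among those dropped. LMIC patients retained: 356 × 0.80 ≈ 285.

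observed LMIC mortality = (0.40 − f × m) / (1 − f)

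| m among dropped | Calculation | Observed LMIC | Gap from 30% | Power |
|---|---|---|---|---|
| 60% | (0.40 − 0.12)/0.80 | 35.0% | 5.0 points | about 27% |
| 50% | (0.40 − 0.10)/0.80 | 37.5% | 7.5 points | about 52% |
| 40% | (0.40 − 0.08)/0.80 | 40.0% | 10.0 points | about 75% |
| 30% | (0.40 − 0.06)/0.80 | 42.5% | 12.5 points | about 91% |

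Power here is the chance of a significant result for the observed contrast with 356 and 285 patients. The 91% in the last row is no gain, because the gap being tested is overstated.

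With f = 0.10 and m = 60%, observed LMIC mortality is (0.40 − 0.06)/0.90 = 37.8% and power is about 57%.

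**Step 4: the top row of the table, with the same exclusion in both settings.** In that row eD = 0.12/0.40 = 30% of deaths and eS = 0.08/0.60 = 13.3% of survivors are removed. Applied to both groups, this gives 25.7% v 35.0%, a gap of 9.3 points, an unchanged odds ratio and power of about 68%. Losing half the gap therefore requires death-related exclusion to be concentrated in LMICs.

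**The case against.** A reader might infer that the rule selectively removes deaths from low-resource settings and so shrinks the gap. The article does not support that. It says only that missing values could affect some centres more than others. It gives no direction, names no income tier and makes no link to death.

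The mechanism may also be weaker than it looks. The rule counts required fields, and the operative section is collected only where applicable, so a patient who dies before surgery may have no operative fields to miss. An investigation that was unavailable might be recordable as not done. The field list is in supplementary material that is not shown, so this cannot be checked. Early death also ends follow-up: "Patients will be followed up until 30 days, death or discharge from hospital, whichever comes first". Such records may be closed sooner than those of long-stay survivors. Each site has an independent validator for key variables, and a pilot was run. Finally, a formal statistical plan is promised, and imputation methods and sensitivity analyses are commonly left to it.

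Most of this stands. It rules out a one-directional claim and any single figure for the bias, and the absence of an imputation method from the article is not a fault. It does not rescue the rule itself. The exclusion is stated twice, applies without exception to the analysis, and has no stated benefit for a mortality comparison. Validation may reduce the number of records affected, but it does not change what happens to a record below the threshold whose outcome is known.

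**Conclusion.** The point holds in limited form. As written, the plan can discard known primary outcomes from its main comparison and so may bias mortality by setting. Size and direction are unknown. In the illustration, observed LMIC mortality runs from 35.0% to 42.5% against a true 40%, with no bias when those dropped die at the same rate as the rest. That range rests on the planning rates, equal groups, a 20% exclusion share in LMICs and none in HICs; only the planning rates come from the protocol. Exclusion unrelated to death would cost power but cause no bias.

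The two thresholds are a real but minor contradiction, affecting only records at exactly 70%. The sample size of 712 is not in error. This should be fixed, with moderate confidence. A stronger rating would need evidence on who falls below the threshold, which the article does not give.

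**What to change.** - For the primary mortality analysis, include every eligible patient with known vital status, however complete the other fields are.
- In the adjusted models, handle missing covariates by multiple imputation or a similar method; the detail can sit in the statistical analysis plan.
- Keep the 70% rule only as a sensitivity analysis. State one threshold in both sections and count it over the fields that apply to the patient.
- Report the number of below-threshold records, and mortality among them, by setting.

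The cost is a wording change in the Eligibility criteria and Statistical analysis sections and a small amount of extra analysis. No new data are needed.

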### Data collection and storage

Data will be collected from consecutive patients who met the inclusion criteria during the study period. The dataset contains five sections: baseline data, imaging data, acute management data, operative or interventional data (if applicable) and outcome data (see online supplemental material). The data points were determined through consultation with clinicians from a range of income settings. Only pseudonymised data will be collected on the online platform, and anonymised data will be accessed by the central study team.

#### Outcome measures

The primary outcome of the study is 30-day mortality or survival to hospital discharge (whichever comes first). Participating centres will be stratified according to income settings, and mortality rates will be compared across cohorts defined by income groups.

Secondary outcome measures include:

perioperative complications, including but not limited to surgical site infections;clinical outcomes other than mortality, measured through:Glasgow coma scale at discharge;modified Rankin scale.Length of hospital stay and intensive care unit stay.

Each unit will be asked to complete a questionnaire on care processes and resources available. This will describe local case load, catchment population and referral pathways, and management frameworks and infrastructure at prehospital and hospital level.

Data will be collected and stored exclusively on a secure web-based system within the Outcome Registry Intervention and Operation Network platform https://orion.net/. This will enable secure data collection, validation and storage in a standard format, which is compliant with the UK National Health Service (NHS) security standards (including the Information Governance Toolkit). All patient data will be recorded and held anonymously. A pilot phase was conducted to assess feasibility prior to rolling out the full study.

### Statistical analysis

A formal a priori statistical plan will be produced for data analysis. In short, the primary analysis will comprise statistical descriptive analysis of patient-level variables and the characterisation of processes of care using descriptions of provider profiling data and patient-level process variables.

Country groups will be defined using the human development index (HDI), a recognised index of human development.^21^ The 30-day mortality will be reported for each HDI tier. Further analyses will stratify against other indices of economic development and health. Multivariable logistic regression models will be used to investigate the primary and secondary outcomes. Provider profile summaries will be compared with current evidence-based best practices to identify gaps and associations with care processes and case mix.

There is limited robust epidemiological data on sICH globally across income settings, with mortality rates for hospital cohorts reported between 20% and 33% in HICs and 39% and 62% in LMICs.^22^,^28^ Therefore, an accurate sample size calculation is not feasible. However, taking conservative mortality estimates indicating a 30-day mortality rate for sICH of around 30% in HICs and up to 40% in LMICs, using an alpha value of 0.05 and power of 80% to show a 10% difference between HIC and LMIC settings, a total of 712 patients would need to be recruited. Subgroup analyses will be performed, for example, to describe differences between sICH subtypes or hospital type.

Based on the data and experience from other observational studies with a similar methodology, we would expect that each centre enrols around three to five patients over a 30-day study period.^19^ Therefore, with around 150 recruiting centres from our pre-existing research network, we would expect to meet and exceed the sample size required. Given the nature of this international study, missing values are expected and could affect some participating centres more than others. Patients with at least 70% data field completeness will be included in the analysis. At each site, a data validator, independent from the primary data collectors, will validate accuracy for key study variables to ensure completeness and data accuracy.

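### Logistic regression is named for every outcome, but hospital and ICU stay are durations ended by death and cut off at day 30, so they need a different model

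*Protocol article*

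**What the plan says.** The Statistical analysis section of the protocol article names one class of model: "Multivariable logistic regression models will be used to investigate the primary and secondary outcomes". It makes no exception by type of outcome.

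The Outcome measures section lists these secondary outcomes:

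- "perioperative complications, including but not limited to surgical site infections", which can be recorded as yes or no;
- "Glasgow coma scale at discharge" and "modified Rankin scale", two ordinal scales, introduced as "clinical outcomes other than mortality, measured through";
- "Length of hospital stay and intensive care unit stay", two durations.

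Study setting and population fixes the observation window: "Patients will be followed up until 30 days, death or discharge from hospital, whichever comes first".

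The sample size assumes a "30-day mortality rate for sICH of around 30% in HICs and up to 40% in LMICs". One of the listed Objectives is to compare short-term clinical outcomes between resource settings. The Statistical analysis section also promises a separate formal analysis plan, which is not shown, and presents its own text as a short summary.

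**The concern.** The model named does not match two of the outcomes it is named for. A length of stay has no natural yes/no form, so a logistic model needs a cut-off. The choice of cut-off is arbitrary and affects the answer.

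The more serious difficulty is how a stay ends. Under the follow-up rule it can end in discharge alive, in death, or by running into day 30. Only the first is a completed stay in the sense that matters for describing care. If the three are pooled, a patient who dies on day 2 counts as a two-day stay. The settings to be compared are expected to differ in mortality, so the pooled measure mixes discharge practice with survival. A reader could then take a shorter stay as greater efficiency when part of it reflects more deaths.

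**Working it through.** **1. The plan's own figure.** With 30% vs 40%, two-sided alpha 0.05, power 80%, equal groups and no continuity correction:

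n per group = [1.960 × √(2 × 0.35 × 0.65) + 0.842 × √(0.30 × 0.70 + 0.40 × 0.60)]² / 0.10² = 1.8866² / 0.01 = 355.9, so 356 per group and 712 in total.

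This reproduces the article's 712. The point below concerns the model for stay and leaves this number alone.

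**2. Matching model to outcome.**

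| Outcome | Type | Does a logistic model fit? |
|---|---|---|
| Mortality | binary | yes |
| Perioperative complications | binary | yes |
| Modified Rankin scale | ordinal | yes, in ordinal form or with a stated cut-off |
| Glasgow coma scale at discharge | ordinal, no value after death | yes in form; needs a rule for deaths |
| Hospital and ICU stay | duration, ended by death, censored at day 30 | only after dichotomising |

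**3. What pooling deaths with discharges does to mean stay.** Let p be mortality, S the mean stay of survivors (capped at day 30) and D the mean time to death among those who die by day 30. Then

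mean stay over all patients = (1 − p)S + pD,

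and raising p from 0.30 to 0.40 with S and D unchanged shifts the mean by 0.10 × (D − S). The shift is negative when deaths come earlier than survivors' discharges, and positive when they come later.

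The article gives neither S nor D, so both are assumed. Survivor stay is lognormal with sigma 0.8 and median 7, 14 or 21 days, giving S = 9.19, 15.92 or 20.29. Time to death is exponential with parameter m = 3, 5, 10 or 20 days, conditioned on death by day 30. Then D = m − 30e^(−30/m)/(1 − e^(−30/m)) = 3.00, 4.93, 8.43 or 11.38. The shift in days is:

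| m (days) | survivor median 7 | 14 | 21 |
|---|---|---|---|
| 3 | −0.62 | −1.29 | −1.73 |
| 5 | −0.43 | −1.10 | −1.54 |
| 10 | −0.08 | −0.75 | −1.19 |
| 20 | +0.22 | −0.45 | −0.89 |

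A simulation of 400,000 patients per scenario agrees, with a range of −1.7 to +0.2 days and shorter stay in 11 of 12. In the middle case (median 14, m = 5) mean stay is 12.6 vs 11.5 days.

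At the extremes of the mortality ranges reported in the article (20% vs 62%), the multiplier is 0.42. The shift then runs from 0.42 × (3.00 − 20.29) = −7.3 to 0.42 × (11.38 − 9.19) = +0.9 days.

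**4. What it does to a dichotomised stay.** Now assume constant hazards: discharge alive 0.07 per day in both settings, death 0.03 vs 0.05 per day.

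- Deaths by day 30: (0.03/0.10)(1 − e^(−3)) = 28.5% vs (0.05/0.12)(1 − e^(−3.6)) = 40.5%.
- Mean stay: (1 − e^(−3))/0.10 = 9.5 vs (1 − e^(−3.6))/0.12 = 8.1 days, a gap of 1.4 days with the same discharge rate.
- Chance of a stay longer than c days: e^(−0.10c) vs e^(−0.12c). For c = 7, 14 and 21 this is 49.7% vs 43.2%, 24.7% vs 18.6% and 12.2% vs 8.0%, giving odds ratios of 0.77, 0.70 and 0.63.

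Under these assumptions a logistic model of long stay reports a difference between settings that have identical discharge rates, and its size moves with the cut-off.

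**5. Survivors only.** In step 3 survivors' stay is the same in both settings because it was set so; that agreement is an input. In step 4, with equal discharge hazards, mean stay among those discharged alive by day 30 is 1/h − 30e^(−30h)/(1 − e^(−30h)), with h the sum of the two hazards. This gives 8.4 days for h = 0.10 and 7.5 for h = 0.12. Restricting to survivors therefore removes the difference under one set of assumptions and not under the other.

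**The case against.** The strongest reply is that the article condenses a formal analysis plan, and that cut-offs, coding of deaths and censoring rules belong there. That stands for the two ordinal scales. Ordinal logistic regression is logistic regression, so the sentence does not exclude a proper model for the modified Rankin scale or the Glasgow coma scale, and a missing cut-off or death rule is no error in an article. It does not cover stay. There the article names a model that does not suit the outcome. An analysis plan that follows the sentence inherits the mismatch, and one that departs from it contradicts the published protocol.

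A second reply is that the primary analysis is descriptive, and that the article nowhere proposes comparing mean stay with deaths included. That is fair. The figures above show what could happen under an analysis the article leaves open, not what it has committed to.

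A reader might also infer that high-mortality settings will look better on stay, or that none of the secondary outcomes suits a logistic model. The documents support neither. The sign of the shift depends on the timing of deaths, about which the article says nothing, and complications are naturally binary. Nor is the modified Rankin scale necessarily truncated by death, since death can be scored as its worst category.

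**Conclusion.** The point holds for hospital and ICU stay. The article assigns them a model that fits only after an arbitrary dichotomisation, and its follow-up rule makes death and day 30 end the observed stay. Where deaths are pooled with discharges, a mortality difference of the planned size can shift mean stay by about −1.7 to +0.2 days with no difference among survivors. These values rest on assumed distributions for stay and time to death, and on equal survivor stay. They indicate the order of magnitude and do not predict the study's result.

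For the two ordinal scales, the present wording is workable once the form of model and the handling of deaths are stated. The matter affects secondary outcomes only. It should be corrected because comparison between settings is an aim of the study and the correction is cheap.

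**What to change.** Amend the sentence in Statistical analysis, and carry the change into the analysis plan:

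- **Mortality and perioperative complications:** binary multivariable logistic regression, as now.
- **Hospital and ICU stay:** time to discharge alive (for ICU, time to leaving the unit alive), with death as a competing event and censoring at day 30. Show cumulative incidence by setting, with a cause-specific or Fine-Gray model for adjusted comparison. The cause-specific model describes the discharge rate among patients still alive in hospital. The cumulative incidence shows how many leave alive and when. The plan should say which it interprets.
- **Modified Rankin scale:** ordinal logistic model with death as the worst category.
- **Glasgow coma scale at discharge:** reported in survivors, beside mortality for the same group.

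The cost is revised wording and slightly more analysis work. It should need no new data if dates of admission, discharge, death, and ICU entry and exit are recorded. The field list is in a supplement not shown, so this should be checked. The sample size of 712 rests on mortality and does not change.

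### The 80% power claimed for 712 patients assumes independent patients split equally between HIC and LMIC settings, and the clustered, open-recruitment design supports neither assumption

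*Protocol article*

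**What the plan says.** The Statistical analysis section sizes the study on a "30-day mortality rate for sICH of around 30% in HICs and up to 40% in LMICs", with alpha 0.05 and "power of 80% to show a 10% difference between HIC and LMIC settings, a total of 712 patients would need to be recruited". It gives no allocation ratio, ICC or design effect. The same section expects about 150 centres to enrol three to five patients each, and it groups countries by human development index (HDI). The Outcome measures section stratifies centres by income setting and compares mortality between the income groups.

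Study setting and population states "Any hospital admitting patients with sICH worldwide is eligible to participate" and sets no target by income group. It treats 712 as a floor: "A minimum sample size of 712 patients will be recruited".

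On the model, the Statistical analysis section says only "Multivariable logistic regression models will be used to investigate the primary and secondary outcomes", and leaves the detail to a separate statistical plan that is not shown.

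**The concern.** The two-proportion formula needs independent patients and, in the form that yields 712, equal groups. Here patients share a centre and a country. The exposure does not vary within either, so the whole design effect falls on the HIC v LMIC contrast that sized the study. The protocol's own objectives are to describe variation in resources, pathways and delays between settings, so an ICC of zero would sit badly with its rationale. Recruitment through existing networks and professional societies, with no target per income group, gives no ground for expecting a 50:50 split.

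At stake is how a reader interprets the mortality comparison. A study described as having 80% power will have a null result read as fairly strong evidence against a 10-point gap. If the real power is nearer 65% to 70%, that reading is too confident.

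**Working it through.** **Inputs from the protocol article.** Mortality 0.30 (HIC) and 0.40 (LMIC), alpha 0.05, power 80%, N = 712, about 150 centres, three to five patients per centre. Sidedness is not stated; two-sided reproduces the figure, while one-sided gives 562.

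**Assumed, because the document gives no value.** ICC 0.01 to 0.10; HIC:LMIC split; variation in centre size; patients per country.

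**Step 1: reproduce 712.** Pooled two-proportion formula, 1:1, no continuity correction:

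n per group = [1.96 x sqrt(2 x 0.35 x 0.65) + 0.8416 x sqrt(0.30 x 0.70 + 0.40 x 0.60)]² / 0.10² = 355.9, rounded up to 356.

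Total = 2 x 356 = 712, and power at 356 per group is 80.0%. The arithmetic is right, with nothing left over for clustering or imbalance.

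**Step 2: clustering by centre, equal groups.** Mean centre size m = 712/150 = 4.75. Design effect DE = 1 + (m - 1) x ICC. Power is recomputed at 356/DE per group, and N for 80% power is 712 x DE.

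| ICC (assumed) | DE | Effective N | Power at 712 | N for 80% |
|---|---|---|---|---|
| 0.01 | 1.038 | 686 | 78.5% | 739 |
| 0.02 | 1.075 | 662 | 77.1% | 766 |
| 0.05 | 1.188 | 600 | 72.9% | 846 |
| 0.10 | 1.375 | 518 | 66.6% | 979 |

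**Step 3: imbalance alone (ICC = 0).**
- 60:40 HIC:LMIC: 78.6%
- 70:30: 73.5%
- 30:70: 72.3%

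**Step 4: both together, 30:70 HIC:LMIC.**
- ICC 0.05: 64.6%
- ICC 0.10: 58.2%

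**Step 5: features that lower power further.**
- Unequal centre sizes: DE = 1 + ((1 + CV²) x m - 1) x ICC. With an assumed CV of 0.8 and equal groups, DE is 1.136, 1.340 and 1.679 at ICC 0.02, 0.05 and 0.10, and power is 74.8%, 67.7% and 57.9%.
- Country-level clustering: with an assumed 20 patients per country and ICC 0.02, DE = 1 + 19 x 0.02 = 1.38 and power is 66.4%.

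**Step 6: can over-recruitment make up the loss?** The protocol's forecast is 150 x 3 = 450 to 150 x 5 = 750 patients. The midpoint, 600, gives 72.9% even with independent patients split 50:50. The top, 750, is below the 846 needed at ICC 0.05 with equal groups.

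**Step 7: if the regression ignored centre clustering.** True two-sided alpha = 2 x (1 - Phi(1.96/sqrt(DE))): 0.059, 0.072 and 0.095 at ICC 0.02, 0.05 and 0.10.

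**The case against.** The protocol is candid about its sample size. It says that an accurate calculation is not feasible, calls its mortality estimates conservative and treats 712 as a minimum. It also describes the primary analysis as descriptive, so no confirmatory decision hangs on 80%. With so few patients per centre, the centre-level loss is small at a low ICC (78.5% at 0.01), as it is at a 60:40 split. No figure in the document establishes a 30:70 split.

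Uncertainty in the rates can outweigh the clustering effect in either direction. At 30% v 45%, 712 patients would give about 94% power even with DE 1.19 and a 30:70 split. At the closest ends of the cited ranges, 33% v 39%, power would be 38% with independent patients in equal groups.

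Much of this stands, and it limits both the size and the severity of the point. It does not rescue the stated power. The caveat about feasibility is explained by poor mortality data, not by clustering or balance, and a specific 80% claim follows it. The minimum gives little room, since the forecast tops out at 750. Comparing mortality between income groups is a stated objective and is what the study was sized for.

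A reader might also infer that the regression will ignore clustering, so that its standard errors will be too small. The document does not support that. It names multivariable logistic regression in a brief summary and defers to an unseen plan, and its wording is compatible with random intercepts, GEE or robust errors. The inflated error rates in Step 7 are a conditional risk, not an error in the protocol.

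**Conclusion.** The number 712 is calculated correctly, but the 80% attached to it holds only for independent patients split 50:50. The protocol states neither condition and its design secures neither, so the unqualified 80% is not supported. Any positive ICC or unequal split takes power below 80% at the assumed rates.

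How far below cannot be known from the document. Over the assumed values above, centre clustering and a split of up to 30:70 give anything from 78.5% down to about 58%, before unequal centre sizes or country-level clustering. It would go too far to say that the study will certainly miss its power by a material amount: at a low ICC and near-equal groups the loss is one or two points. Severity is moderate, because the remedy is wording and the primary analysis is descriptive.

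**What to change.** In the Statistical analysis section:

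1. State that 712 assumes independent patients and a 1:1 HIC:LMIC split.
2. Replace the unqualified 80% with power at 712 over a stated range of ICC and HIC:LMIC split. Label both as assumptions, and name the assumptions on centre size and country clustering. The tables above could serve as a starting point. A single narrow range would be misleading, since the answer depends on both inputs.
3. As a safeguard, add a sentence saying that the regression comparing income or HDI groups will account for clustering by centre and country, through random intercepts, GEE or cluster-robust errors.

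The cost is a change of wording, a less favourable stated power and, if a clustered model was not already intended, wider confidence intervals. No extra patients are required.
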